### 3.5. Statistical Methods for Primary and Secondary Outcomes

Caries activity levels after implementing the daily tooth-brushing scheme will be evaluated as the primary outcome. The outcomes will offer information regarding the particularities of the clinical investigation for the specific age group and the time necessary for the investigation and intervention. Clinical outcomes will be evaluated by using the caries incidence rate, calculated on each tooth as the unit of analysis and evaluated using a multi-step approach:

The net caries increment for initial, moderate, and extensive caries severity using ICDAS (Δ-initial, Δ-moderate, and Δ-extensive) will be calculated at each follow-up examination.

Events will be defined as a tooth receiving a lesion or as the sum of the Δ-caries changes in status recorded at the baseline examination, at the interim, and at the last examination. The number of events will be appraised by subtracting the number of caries-free teeth at the last examination from those at baseline.

Data analysis will be performed using SPSS version 24 (IBM Corp., Armonk, NY, USA) and the R software (R Core Team 2023). SPSS will be used for initial data cleaning, descriptive summaries, and basic inferential tests. R will be used for advanced modeling, intention-to-treat (ITT) analyses, and reproducible visualizations.

Data will be cleaned and validated prior to analysis. Descriptive statistics will be computed using continuous variables—mean ± SD (if normal), or median [IQR] (if non-normal) and categorical variables—counts and percentages. Baseline comparability between groups will be assessed but not tested for statistical significance (in accordance with CONSORT guidelines) [19]. Primary outcomes will be analyzed using the intention-to-treat (ITT) principle. The choice of statistical test depends on the outcome type. For continuous outcomes, linear regression adjusting for baseline, if available, will be used. Logistic regressions will be performed for binary outcomes and Poisson or negative binomial regression could be used for count data. For the longitudinal data, linear mixed models or generalized estimating equations (GEE) will be used to account for within-subject correlation. To explore relationships between secondary variables, correlation analysis will be performed.

The non-parametric Mann–Whitney U test will be applied to assess the differences across the mean number of events between groups.

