The efficacy of the treatment will be assessed following the indication of the CONSORT consensus guidelines including both PP (Per Protocol) and ITT (Intention to Treat) protocols to calculate the reduction in risk ratio (RR) and the related number needed to treat (NNT) value. An event will be defined as the change in status at tooth level, i.e., the development of a new lesion or the progression of an existing lesion to a more severe stage. Cox Proportional Hazards models will be run to assess the factors associated with caries change in status. Estimates will be reported in the hazard ratio (HR) and their respective 95% confidence interval (95%CI). For all the statistical analyses, the statistical significance will be set at α < 0.05.

The extent and pattern of missing data will be explored. If data are missing at random, multiple imputations will be used. Sensitivity analyses will compare complete cases with imputed datasets. A two-sided alpha level of 0.05 will be considered statistically significant. For multiple secondary outcomes, false discovery rate (FDR) or Bonferroni correction may be applied. The results will be presented with appropriate tables and figures, for reproducibility.

A major aim of the monitoring and evaluation is to collect data to inform and support the planned longer-term roll-out of the program. Process evaluation will, therefore, be a major component of the evaluation plan, as well as using statistical methods for analyzing primary and secondary outcomes and the reference to where other details of the statistical analysis plan can be found, if not in the protocol.

An assessment of the costs of managing dental caries will be obtained through the triangulation of information collected from the National Insurance House and cost data sourced online. Given the variation in the provision of subsidized care across Romanian regions and the scarcity of information on public sector health care costs, private treatment costs are used as a proxy to estimate the direct costs of dental caries.

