## 4. Expected Outcomes

The primary outcome of the trial will be the assessment of caries incidence, defined as the change in status according to the ICDAS index within the age groups. In addition, data analysis from the trial will provide information on children’s self-assessment of oral health practices and promote oral health activities for children with a focus on age-appropriate key messages and practical preparation for the implementation of the nursery intervention, which consists of a toothpaste/toothbrush scheme with free daily tooth brushing for every 4–6-year-old child attending the nursery. Depending on the region, by using the County Development Index, differences between regions will be assessed in order to establish the efficacy of the program at the national level.

Secondary outcomes will be the skills gained by dental hygienists to deliver oral health promotion to nursery nurses after specific training, and a comprehensive process of parental information and consent and validation that shapes healthy behaviours throughout life.

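### Section 3.5 counts events as baseline minus final caries-free teeth, which cannot register progression, nets reversals against new lesions, and conflicts with the tooth-level event definition in the same section

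*Protocol article*

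**What the plan says.** All the event rules stand in the protocol article, section 3.5. The outcome frame comes first: "Clinical outcomes will be evaluated by using the caries incidence rate, calculated on each tooth as the unit of analysis". Net increments are then to be calculated at each follow-up for initial, moderate and extensive lesions. Three statements about events follow:

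- A definition with two alternatives: "Events will be defined as a tooth receiving a lesion or as the sum of the Δ-caries changes in status".
- Directly after it, a counting rule: "The number of events will be appraised by subtracting the number of caries-free teeth at the last examination from those at baseline".
- Further down, after the sentence on the risk ratio and number needed to treat, a change in status at tooth level, explained as "the development of a new lesion or the progression of an existing lesion to a more severe stage".

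The count is then compared between groups: "The non-parametric Mann–Whitney U test will be applied to assess the differences across the mean number of events between groups".

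Section 4 states: "The primary outcome of the trial will be the assessment of caries incidence, defined as the change in status according to the ICDAS index". Section 2 lists the arrest of caries progression among the things to be evaluated.

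**The concern.** A count of events should follow the definition of an event. The subtraction is a difference between two whole-mouth totals. It sees only whether a tooth is in the caries-free total, so worsening within the carious range is lost. It also adds gains and losses of caries-free teeth together, whatever caused them.

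Two things are at stake. First, the trial means to evaluate arrest of progression and takes change in ICDAS status as its primary outcome, yet one stated count is blind to progression. This is not a rare situation in the target population: section 5 reports that only 14% of 6-year-olds in the national survey had a dmft of 0, so 86% had at least one affected tooth (decayed, missing or filled). Second, with several event rules in one section, the same data can yield different results depending on which rule the analyst applies, and the article does not say which one governs.

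**Working it through.** The article gives no figure for the event count, so there is none to reproduce. The check compares the two rules algebraically and then on constructed mouths. The tooth numbers below are assumptions chosen to isolate each mechanism; they are not trial data.

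**Algebra.** For one child, between baseline and the last examination, let:

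- N = sound teeth that develop a lesion
- P = carious teeth that move to a more severe stage
- R = carious teeth that revert to sound
- L = sound teeth no longer present
- E = sound teeth newly present

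Subtraction rule: D = (caries-free at baseline) − (caries-free at last) = N − R + L − E.

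Tooth-level definition: T = N + P.

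Difference: D − T = L − E − R − P.

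If the count is limited to teeth present at both examinations, L = E = 0 and D − T = −(R + P). The rules then agree only if no tooth progresses and none reverts.

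**Constructed mouths.**

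| Case | Baseline − last caries-free | D | T |
|---|---|---|---|
| 14 sound, 6 carious; all 6 progress | 14 − 14 | 0 | 6 |
| 16 sound, 4 initial lesions; 2 new lesions, 2 reversals | 16 − 16 | 0 | 2 |
| 20 sound; 3 new lesions, nothing else | 20 − 17 | 3 | 3 |
| 20 sound; 4 sound teeth shed, not yet replaced | 20 − 16 | 4 | 0 |
| 20 sound; 4 new lesions, 4 sound teeth erupt | 20 − 20 | 0 | 4 |
| 20 sound; 1 new lesion, 4 sound teeth erupt | 20 − 23 | −3 | 1 |
| 16 sound, 4 carious; the 4 are replaced by sound teeth | 16 − 20 | −4 | 0 |

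The first three rows use a fixed set of teeth and need no fact from outside the article. The last four apply only if the subtraction runs over whatever teeth are present at each examination.

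**Do the last four rows matter here?** The Study Setting section enrols children aged 4–6 years, and the Abstract gives 24 months, so children would be about 6–8 years old at the end. That primary teeth are shed and permanent teeth erupt around these ages is general knowledge; the article does not discuss it. Section 3.5 does not limit the subtraction to teeth present at both examinations. A negative count could not enter the Poisson or negative binomial regression that the section offers for count data.

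**The case against.** The strongest reply is that the subtraction is one step in a multi-step evaluation. Progression is not lost to the plan as a whole: the increments by severity and the later tooth-level definition both capture it. That is right, and the point is confined to the subtraction and to its conflict with the rest of the section. The article does not itself call the subtraction the primary event count, and its link to the Mann–Whitney test is inferred from the shared term for number of events.

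Netting, it can also be said, is openly declared, since the section names a net increment, and the article expects fluoride to reverse early lesions. A net increment is a legitimate measure. It is still not the number of new or progressing lesions, which is what the later definition counts.

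The treatment of shed and erupted teeth is commonly left to an analysis plan, which is not shown. This stands in part. A plan restricting the count to teeth present at both examinations would remove that problem, so it is stated here as conditional. It would not remove the blindness to progression, the netting or the contradiction.

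A reader might infer that the risk ratio, the number needed to treat and the hazard ratio are distorted too. The text does not support that: the tooth-level definition stands between the risk ratio sentence and the Cox model sentence, and the natural reading is that these measures use it.

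A reader might also try to express the problem as lost power. Section 3.2 states no effect size. One can be back-solved from 415 children, SD 2, design effect 2 and an assumed two equal arms: 2 × (1.96 + 1.28) × √(2/103.75) = 0.90. But the article does not say that the SD of 2 belongs to this count, and any extra spread from shedding and eruption would have to be assumed. No power loss is claimed.

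**Conclusion.** Section 3.5 is wrong as written and should be corrected. The subtraction rule and the tooth-level definition are inconsistent. On a fixed set of teeth the subtraction falls short of the tooth-level count by exactly the number of progressions plus the number of reversals to sound, for example 0 against 6 when six carious teeth all worsen. This follows from the text alone.

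That shed sound teeth count as events, and erupted sound teeth cancel them, holds only if the subtraction is taken over all teeth present at each examination. That is the literal reading, but an unseen analysis plan could narrow it. The size of the effect on the between-group comparison cannot be given, because the article supplies no rates of progression, reversal, shedding or eruption.

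**What to change.** - Delete the subtraction rule from section 3.5, and use the tooth-level definition (new lesion or progression) for every event-based analysis, including the Mann–Whitney test. Remove the two-way alternative in the preceding sentence as well.
- Count events by matching each tooth between examinations, on one stated severity scale, for example the initial, moderate and extensive grouping already in the section.
- Stop following a naturally shed tooth at its last examination, and let a newly erupted tooth enter at its first.
- State whether fillings and extractions because of caries count as events. The tooth-level definition does not mention them, so this is a decision still to be made.
- Fix one denominator, either teeth at risk or tooth-time at risk.
- Report reversals separately, or through the net increment already planned.

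The cost is protocol wording and programming. The tooth is already the unit of analysis, so the charting should largely support this. The one addition to data collection is a code for why a tooth is absent. It has to be recorded at the examination, so it should be settled early.

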The number of children is based on an initial calculated requirement of 415 participants, with an additional 10% (rounded up from 456.5 to 460) added to account for potential dropouts or loss to follow-up. The sample is stratified based on administrative units and locality type and randomization is ensured by using the MS Excel function. Children will be included based on the enrolment in kindergarten, consent of the parents, and assent from the child. The exclusion criteria are represented by chronic general diseases or a history of allergic reactions, the presence of fluorosis or other enamel deficiencies, and non-collaborative behavior. The selection can be seen in the flowchart in Figure 1.

The nationally representative sample will be evaluated at baseline using self-assessment tools and clinical examination. During the intervention, evaluations will be performed every 6 months.

The program is designed to deliver additional clinical prevention activities through dental hygienists, aimed at children aged four to six, a special priority being afforded to nursery establishments, in order to improve the oral health of young children and complement the established national toothpaste/toothbrush scheme. The activity flow chart can be seen in the figure below (Figure 2).

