### 3.2. Sample Size

The sample size calculation results in a sample of 460 children aged 4–5 years, considering the following parameters: a type I error of 0.05 (z 1 − alpha/2  =  1.96), power of 0.9 (z 1 − beta  =  1.28), standard deviation (SD) 2, a design effect of 2, and a drop-out rate of 10%. For the odds ratio, a percentage mean difference between groups was used as suggested by literature when significance is found after intervention usually measuring for caries prevalence or increment, with mixed interventions ranging from fluoride varnish and teaching how to properly brush teeth to motivational techniques and oral health education [16,17,18]. Demographics with respect to the region and age of interest were chosen.

The total sample size was calculated according to the WHO guidelines using a stratified sampling technique for examination sites in Romanian cities: Bucharest, Timișoara, Cluj-Napoca, Craiova, Iasi, Targu Mures, and the surrounding geographical areas. Data collection points will be 4 kindergartens in the Capital or metropolitan areas, 2 kindergartens in each of 2 large cities, and 1 kindergarten in each 4 villages from different geographic areas (Dobrogea, Moldova, Ardeal, and Muntenia). Metropolitan areas in Romania are Iași, Brașov, Oradea, Târgu Mureș, Cluj Napoca, Craiova, Roman, Baia Mare, Satu Mare, Timișoara, and Arad.

Data will be collected from 3 types of residential areas: metropolitan areas (150 evaluations), big cities (150 evaluations), and rural areas (100 evaluations). In metropolitan areas and big cities, 25 children will need to be evaluated in the same kindergarten.

In rural areas, more than one kindergarten can be evaluated until the desired number of evaluations is obtained for the specific region. This principle has been added because kindergarten is not mandatory in Romania and the number of children enrolled in kindergarten in rural areas is quite low in some regions of the country.

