### 3.3. Assignment of Interventions

In order to create a nationally representative sample, the public information available on the websites of all County School Inspectorates (41 counties plus the Romanian Capital) was analyzed. This process involved the evaluation of publicly available information from 4696 schools, which aided the understanding of the territorial distribution of the target population.

The national representative sample is stratified and randomized. The stratification was performed at the level of administrative units (counties), and on locality type (i.e., urban versus rural localities). For each county, the total number of pupils and the percentage of children for each of these administrative units were computed. The percentage was used to estimate how many children would have to be included in each county. The number was then divided based on locality type (i.e., urban versus rural), and the final target number of evaluations was obtained. The MS Excel’s randomization function was used for each county to select an urban and a rural nursery.

The steps of the allocation sequence are as follows:The order of the counties is decided—each collection point receives several counties and the research team can decide in which county it would be more convenient.Kindergartens in the respective county are contacted to determine their availability to participate in the study and the number of children from the target population available for evaluation.If the 2 kindergartens that are contacted together have at least 18 children (out of the required 25), data collection can begin in the respective county.

If the 2 kindergartens contacted do not have at least 18 children together, the next county on the list will be selected and the procedure returns to steps 2 and 3.

E-mails will be sent to the correspondence address provided to generate the allocation sequence. Consent in principle and an estimate of the number of children in the target population will be requested. If there is no response within the next 5 working days, the kindergarten will be called in to check that the e-mail was received in good condition (e.g., to obtain a working e-mail address or to see the status of the request).

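### No stated between-group analysis adjusts for locality type, although the sample is stratified by it and nothing stated balances it between groups

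*Protocol article*

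**What the plan says.** Section 2 (Experimental Design) states: "The sample is stratified based on administrative units and locality type and randomization is ensured by using the MS Excel function". Section 3.3 (Assignment of Interventions) repeats it: "The stratification was performed at the level of administrative units (counties), and on locality type". There the aim is a nationally representative sample, and the Excel function picks an urban and a rural nursery in each county. Section 3.2 sets targets by residential type: 150 evaluations in metropolitan areas, 150 in big cities and 100 in rural areas.

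Section 3.5 lists the analyses:
- For continuous outcomes: "For continuous outcomes, linear regression adjusting for baseline, if available, will be used".
- Logistic, Poisson or negative binomial regression for binary and count outcomes, with no covariates named.
- Mixed models or GEE, for correlation within a subject.
- For the event count: "The non-parametric Mann–Whitney U test will be applied to assess the differences across the mean number of events between groups".
- Risk ratio and number needed to treat, and Cox models for factors associated with change in caries status.

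None names county, locality type or kindergarten. Residence, type of city and development index appear in section 3 (Procedure) as risk factors to relate to the clinical indices. The County Development Index returns in section 4, for differences between regions.

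**The concern.** The Discussion describes marked inequalities in oral health and ties oral health to socio-economic status, education and access to care. Section 3 treats the place of residence as one of the elements that may explain caries. On the document's own account, locality type is therefore a likely prognostic factor, and it is known for every child from the way sites are chosen.

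There are few kindergartens. If groups differ by chance in their share of rural kindergartens, that difference enters the estimated effect, and the stated analyses remove it only so far as baseline caries carries it. The Mann–Whitney test removes none of it. At stake are the credibility of the effect estimate under a chance imbalance and, depending on the unit of allocation, some precision.

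**Working it through.** **1. The plan's own figure.** Inputs from section 3.2: "a type I error of 0.05" (z = 1.96; section 3.5 confirms two-sided), power 0.9 (z = 1.28), and "standard deviation (SD) 2, a design effect of 2, and a drop-out rate of 10" per cent. No numerical effect is given; the text says only: "For the odds ratio, a percentage mean difference between groups was used as suggested by literature". The 415 therefore cannot be derived from the stated inputs alone. Back-solving gives a difference of 0.90:
- per group: 2 × 2² × (1.96 + 1.28)² / 0.9² = 103.68
- two groups, design effect 2: 103.68 × 2 × 2 = 414.7, i.e. 415
- drop-out: 415 × 1.1 = 456.5, rounded in the plan to 460.

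**2. Implied clustering.** Section 3.2 asks for 25 children per kindergarten in metropolitan areas and big cities. With design effect 2, ICC = (2 − 1)/(25 − 1) = 0.042. About 4% of a child's outcome variance lies between kindergartens, but 25 × 0.042/2 = 52% of the variance of a kindergarten mean does. At 35 children and the same ICC the share is 35 × 0.0417/(1 + 34 × 0.0417) = 60%.

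**3. Number of kindergartens.** The data collection points give 4 + 2 × 2 + 4 = 12. The 400 targeted evaluations at 25 each would need 16.

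**4. Chance imbalance.** Assumption: 12 kindergartens, 4 of them rural, simple 6:6 allocation of kindergartens.
- All allocations: C(12,6) = 924.
- Rural split 3:1: 2 × C(4,3) × C(8,3) = 448. Rural split 4:0: 2 × C(8,2) = 56.
- Chance of 3:1 or worse: 504/924 = 55%. Chance of 4:0: 56/924 = 6%.

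**5. If children are allocated within kindergartens.** N = 415, SD 2. Suppose the strata explain all between-kindergarten variance, the most favourable case. The residual SD falls from 2.00 to 2 × √(1 − 0.042) = 1.96.

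| Difference | Power, unadjusted | Power, adjusted |
|---|---|---|
| 0.9 | 99.6% | 99.7% |
| 0.6 (assumed) | 86.3% | 87.7% |

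At 0.6 the adjusted figure is 87.0% for ICC 0.02 and 89.6% for ICC 0.10.

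**6. If kindergartens are allocated and the analysis is valid at that level.** If locality explains a share R² of the between-kindergarten variance (assumed; the document gives no figure), the variance of a kindergarten mean is multiplied by 1 − 0.52 R². Three locality types cost 2 degrees of freedom. With 12 kindergartens, t goes from 2.228 (10 df) to 2.306 (8 df), a penalty of (2.306/2.228)² = 1.071.

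| R² | Variance factor | Times 1.071 |
|---|---|---|
| 20% | 0.896 | 0.96 |
| 30% | 0.844 | 0.90 |
| 50% | 0.740 | 0.79 |

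Break-even: (1 − 1/1.071)/0.52 = 13% at 25 children, and (1 − 1/1.071)/0.60 = 11% at 35. Adding the development index costs a third degree of freedom: (2.365/2.228)² = 1.13, with break-even near (1 − 1/1.13)/0.52 = 22% for locality and index together.

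**7. If kindergartens are allocated and clustering is ignored.** The true type I error is 2 × [1 − Φ(1.96/√2)] = 16.6%. A simulated Mann–Whitney test (16 kindergartens of 25, 3000 runs) gave 16.7%. If locality explains 25, 50 or 75% of between-kindergarten variance and is adjusted for, the error is still about 13.9, 11.1 or 8.1%.

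**The case against.** The strongest reply is that these are sampling strata. Section 3.3 uses them to build a representative sample and to pick nurseries, and no section says that allocation to intervention or control was stratified. A reader might infer that the plan breaks the rule that strata used in randomisation belong in the analysis, or that it forfeits precision gained by stratified allocation. The documents support neither. What stands on the other side is that unstratified allocation leaves locality type unprotected, so adjustment is the remaining safeguard.

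A reader might also infer that known variation is simply left in the error, at a cost of 10 to 26% in variance. Those figures are the reductions in step 6 before the degrees-of-freedom penalty. They need an assumed R² and a kindergarten-level analysis that the plan does not state. With children allocated within kindergartens the loss is small. With kindergartens allocated and clustering ignored, the variation is missing from the standard error altogether. Baseline adjustment in the linear model would also absorb part of any stable locality difference, and step 6 gives no credit for that.

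Finally, a full covariate list is commonly left to an analysis plan, section 4 links the County Development Index to judging efficacy nationally, and the Cox models may include such factors. That tempers the point. But section 3.5 does name its adjustment, and it commits to a test that adjusts for nothing; an analysis plan that follows it inherits both.

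**Conclusion.** The point holds in a limited form. Locality type shapes the sample and is plausibly prognostic, yet no stated comparison of groups adjusts for it and nothing stated balances it between groups.

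The size turns on the unit of allocation, which the article does not state. With children allocated within kindergartens, the gain is about 0.1 points of power at a difference of 0.9 and at most about 1.4 points at 0.6, for ICC 0.042. With 12 kindergartens allocated and a valid cluster-level analysis, adjustment pays once locality explains about 11 to 13% of between-kindergarten variance; at an assumed 30% the squared interval width falls by about 10% net. Protection against a chance rural imbalance comes in addition.

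Locality adjustment does not answer the separate mismatch between a design effect of 2 in the sample size and models described only for within-subject correlation. It should not be presented as doing so.

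**What to change.** In section 3.5:
- Include locality type (metropolitan, big city, rural) as a fixed effect in every between-group model, besides baseline caries.
- Replace the Mann–Whitney test with a model-based comparison, or with a rank test stratified by locality type (van Elteren). If kindergartens are allocated, apply the rank test to kindergarten-level summaries, because stratifying by locality does not account for clustering.
- Add a kindergarten random effect or cluster-robust variance, with a small-sample correction given the few kindergartens, and state the unit of allocation.
- Keep the county development index as an optional sensitivity covariate.
- Do not condition on county-by-locality cells. With one urban and one rural nursery per county, a cell is about one kindergarten, and under kindergarten allocation it would absorb the treatment contrast.

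The cost is wording and 2 kindergarten-level degrees of freedom, about a 7% penalty with 12 kindergartens if kindergartens are allocated. Locality type is already known for every site.

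### The sample size assumes a design effect of 2, but no analysis in section 3.5 has a kindergarten term, and the tooth-level analyses state no allowance for teeth within a child

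*Protocol article*

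**What the plan says.** **Design.** Section 3.2 (Sample Size) lists "standard deviation (SD) 2, a design effect of 2, and a drop-out rate of 10" per cent among its inputs and has 25 children examined in each kindergarten in metropolitan areas and big cities. Sections 3, 3.1 and 4 describe a brushing and education scheme run through the kindergarten for all attending children in the age range, with training and brochures for its educators. Section 3.3 (Assignment of Interventions) uses a random function to select nurseries. It does not say what unit is assigned to which arm.

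**Analysis.** Section 3.5 has the caries incidence rate "calculated on each tooth as the unit of analysis". It names linear, logistic and Poisson or negative binomial regression and, for longitudinal data, says that "linear mixed models or generalized estimating equations (GEE) will be used to account for within-subject correlation". A Mann–Whitney U test compares the number of events between groups. Per-protocol and intention-to-treat analyses are used "to calculate the reduction in risk ratio (RR) and the related number needed to treat (NNT) value", with the event defined as a change in status of a tooth. In addition, "Cox Proportional Hazards models will be run to assess the factors associated with caries change in status". None of these is given a kindergarten term, a frailty or a cluster-robust variance.

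**The concern.** Children in one kindergarten share educators, routine, neighbourhood and the delivery of the intervention, and the design effect in section 3.2 is most naturally an allowance for this. The sample is enlarged for clustering, but the analysis as described does not use that allowance. If whole kindergartens form the arms, standard errors computed as if children were independent are too small and the test rejects too often. Teeth within a child add a second level of correlation, which the Cox, RR and NNT analyses do not mention. The primary outcome is affected, and section 3.5 says that the data are meant to support a longer-term roll-out, so a false claim of benefit would have consequences.

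**Working it through.** **1. The plan's own sample size.** Section 2 gives "an initial calculated requirement of 415 participants, with an additional 10% (rounded up from 456.5 to 460". The drop-out step reproduces: 415 × 1.10 = 456.5, rounded to 460. The 415 cannot be derived directly because no effect size is given; section 3.2 says only "For the odds ratio, a percentage mean difference between groups was used as suggested by literature". The two-means formula with SD 2, z-values 1.96 and 1.28 and design effect (DE) 2 is:

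N = DE × 4 × SD² × (1.96 + 1.28)² / δ² = 2 × 4 × 4 × 10.4976 / δ² = 335.9 / δ²

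Setting N = 415 gives δ = 0.90; with δ = 0.90 exactly, N = 414.7, or 415 rounded up. So 415 fits a two-arm comparison of child-level means that already contains the factor of 2. The 0.90 is inferred, not stated. The same 415 without a design effect would fit δ = 0.64, so this is supporting evidence, not proof.

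**2. Implied correlation.** With DE = 1 + (m − 1) × ICC, m = 25 and DE = 2, ICC = 1/24 = 0.042.

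**3. Whole kindergartens allocated, kindergarten ignored.** Section 3.5 states: "A two-sided alpha level of 0.05 will be considered statistically significant". The true level is then 2 × (1 − Φ(1.96/√DE)).

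| DE | True type I error | Coverage of the 95% interval |
|---|---|---|
| 1.5 | 11.0% | 89.1% |
| 2 (plan) | 16.6% | 83.4% |
| 2.5 | 21.5% | 78.5% |
| 3 | 25.8% | 74.2% |

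At DE 2, intervals are 1 − 1/√2 = 29% too narrow.

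**4. Simulation check.** Normal outcome, SD 2, no true effect, DE 2, whole kindergartens allocated, 4,000 replicates. Sections 2 and 3.2 list 4 + 2×2 + 4×1 = 12 kindergartens; the 400 evaluations at 25 each would imply 16.

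| Layout | t-test on children | Mann–Whitney on children | t-test on kindergarten means |
|---|---|---|---|
| 16 × 25 | 17.7% | 17.2% | 5.7% |
| 12 × 35 | 17.2% | 17.0% | 5.1% |

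**5. Children allocated within kindergartens.** With 16 kindergartens of 26, half of each in each arm, and ICC 1/24, the child-level t-test rejected in 4.3% of 3,000 replicates. The inflation in steps 3 and 4 does not arise here.

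**6. Teeth treated as independent, whole children allocated.** The documents give neither the number of teeth nor the within-child ICC. Assuming 20 teeth, DE = 1 + 19 × ICC:

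| Assumed ICC | DE | True type I error |
|---|---|---|
| 0.05 | 1.95 | 16.0% |
| 0.1 | 2.9 | 25.0% |
| 0.2 | 4.8 | 37.1% |
| 0.3 | 6.7 | 44.9% |

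These figures concern tooth clustering alone, and only analyses that make no allowance for it.

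**The case against.** - **The unit of allocation is unstated.** The article calls the study an RCT, section 3.3 describes selection, and the design flowchart is not shown. Delivery to a kindergarten is not the same as allocation of a kindergarten. This stands, so the 16.6% is conditional.
- **The purpose of the design effect is unstated.** Section 3.2 gives no ICC and also refers to WHO stratified sampling. Clustering is the natural reading, but it is a reading.
- **An analysis plan may supply the missing level.** Mixed models and GEE can take a kindergarten term without contradicting the article, and random-effect structure is often left to the analysis plan. This stands in part. The article does, however, fix the unit of analysis, the tests and the one correlation to be modelled, and an analysis plan that followed it literally would omit kindergarten.
- **Stronger tooth-level readings do not hold.** A reader might multiply the tooth and kindergarten design effects and conclude that the primary comparison has a false-positive rate of 42% to 59%. The documents do not support that. The event count for the Mann–Whitney test reads naturally as a per-child count, which already absorbs teeth within a child. The mixed models or GEE are expressly meant to handle within-child correlation. The Cox model is described as an analysis of associated factors, not clearly as the primary between-arm test.
- **NNT.** A reader might infer that the NNT will be a number of teeth. The event is at tooth level, but no denominator is stated for RR or NNT, so the unit is open, not shown to be wrong.

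**Conclusion.** The inconsistency is real: section 3.2 allows for a design effect of 2, and nothing in section 3.5 carries it into the analysis. Its size depends on an allocation unit that the article does not state.

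- **Kindergartens allocated**, as the mode of delivery and the design effect suggest: about 16.6% type I error instead of 5% for any between-group analysis that ignores kindergarten, assuming the plan's DE of 2 is correct; 11.0% to 25.8% for DE 1.5 to 3.
- **Children allocated within kindergartens**: no such inflation. Cox, RR and NNT analyses that treat teeth as independent remain anti-conservative, for example 25% to 45% type I error with 20 teeth and an ICC of 0.1 to 0.3, all three being assumptions from outside the documents.

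It cannot be said without condition that every p-value will be wrong.

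**What to change.** In section 3.5:

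1. State the unit of allocation to arms.
2. If it is the kindergarten, add a kindergarten random effect or kindergarten-clustered variance to all between-group models, with a small-sample correction. With 12 to 16 clusters, the t critical value on 10 to 14 degrees of freedom is 2.23 to 2.14, not 1.96.
3. In that case also replace the Mann–Whitney test with a kindergarten-level permutation test or a clustered rank test.
4. In tooth-level models, including Cox, nest teeth within children (and children within kindergartens), or use variance clustered at the highest level.
5. State the denominator of RR and NNT, and report NNT per child.

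The cost is a few sentences and slightly more complex R code. Intervals become wider. No new data are needed.
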